### Power Estimation

A lower-bound probability of detecting effects in clinical research (power) of 0.80 has been suggested (Cohen, 1988). To get some idea of the statistical power in the present study, we estimated the necessary number of observations (*n*) for achieving a power of 0.80 of detecting a medium effect (Cohen’s *d* = 0.5) using an alpha level of 0.05 for three common tests: Calculations of statistical power were performed with G^∗^Power (Buchner and Erdfelder, 1996). All other statistical analyses were conducted with SPSS.

The primary outcomes in the two groups were compared using analysis of covariance (ANCOVA) with pre-treatment values as the covariate. Making the conventional assumptions of no treatment by pre-treatment interaction, this may be formulated as:

(1)$${\text{Post}}_{\text{i}}=\alpha +\beta_{1}^{*}{\text{Treatment}}_{\text{i}}+\beta_{2}^{*}{\text{Pre}}_{i}+\varepsilon_{\text{i}}$$

The treatment-effect may be estimated by the increase in explained variance when including the Treatment effect in the model. Using *d* = 0.5 this corresponds to an increase in *R*^2^ of 0.06. Assuming a rejection criterion (alpha) of 0.05 and a desired power of 0.80 of detecting an increase in *R*^2^ of 0.06, the estimated required sample size is 62 patients per treatment condition.

The design also included a dichotomous “trauma” condition (see section “Introduction”). Reasoning as above the model may be formulated as:

(2)$${\text{Post}}_{\text{i}}=\alpha +\beta_{1}^{*}{\text{Treatment}}_{\text{i}}+\beta_{2}^{*}{\text{Trauma}}_{\text{i}}+\beta_{3}^{*}{\text{(Treatment}}_{\text{i}}^{*}{\text{Trauma}}_{\text{i}}\text{)}+\beta_{4}^{*}{\text{Pre}}_{i}+\varepsilon_{\text{i}}$$

The effect of interest, the Treatment by Trauma interaction, will be estimated by the increase in explained variance when including this effect in the model over a model with all other effects included. Assuming a rejection criterion (alpha) of 0.05 and a desired power of 0.80 of detecting an increase in *R*^2^ of 0.06, the estimated required sample size is 64 patients per treatment condition. The statistical power of the present study with total *N* = 144 thus appears adequate.

As there seems to be no single standard for power analysis within disaggregating between patient effects from the effect of individual patients using longitudinal mixed models, we did not conduct further power, or sample size for this analysis.

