However, up to 50% of patients with ED do not recover after CBT (Wilson et al., 2007). The highest probability of poor treatment outcomes in patients with ED has been observed in those who experienced childhood sexual abuse and exposure to violent acts at an early age (Mahon et al., 2001; Rodriguez et al., 2005). A study showed that the risk of dropout or relapse rates was, respectively, 10 and 3 times greater among patients with ED who reported previous traumatic events compared with those patients without a history of trauma (Rodriguez et al., 2005). Our own study revealed that childhood sexual abuse and avoidant personality disorder predicted non-response course for patients with longstanding ED who received CBT (Vrabel et al., 2010). Considering the poor outcome and high dropout and relapse rates for these patients, there is a need to develop treatments tailored for patients with ED with trauma histories. To date, however, no treatment approaches for this population have been empirically tested.

When individuals endure early experiences of traumatic experiences they can become more prone toward self-criticism and to develop shame, a hurtful emotional condition characterized by perceiving oneself as a failure (Gilbert, 1998). They may try to regulate their feelings of inadequacy with strategies which ease their pain for a limited time. Accordingly, ED symptoms such as restriction, binging, and compensating behavior such as purging and excessive exercising, could be viewed as efforts to protect themselves and to control underlying feelings of shame (Goss and Gilbert, 2002). ED symptoms are effective at reducing shame in the short-term, but ultimately intensify these feelings in the long-term (Goss and Allan, 2009). Studies have shown that shame and self-criticism have been shown to be a major vulnerability and maintaining factor both for ED and posttraumatic stress disorder (PTSD) (Lee et al., 2001; Irons and Gilbert, 2005) and decreased self-criticism and increased self-compassion has been found to be particularly beneficial in reducing psychological distress and improving well-being (Lutz et al., 2004; Gilbert, 2007; Hoffart et al., 2015). CFT is a transdiagnostic psychotherapeutic approach that seeks to help shame-prone highly self-critical individuals to improve an attitude of inner-kindness and self-compassion (Gilbert, 2005, 2010). Indeed, this treatment should therefore be particularly suitable for a population with ED and childhood trauma.

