### Randomization

Patients will complete the baseline measures and after having signed an informed consent, a researcher blind to the study condition will conduct the random assignment procedure. A blocked randomization procedure will be used to ensure that there will be assigned an equal number of patients with trauma and non-trauma to each condition. Hence the blocks are in pair, such as two trauma patients and two non-trauma patients will be randomly assigned to each condition. The probability for each patient to end up in any of the two conditions will be kept constant at 0.5.

Researchers in the study will be blind to trauma category and the patient’s allocation to the groups. Because of the nature of the treatment content and procedures, therapists, and patients will not be blinded to the group allocation. Patients are informed about their group allocation after completing the pre-care evaluation.

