### Statistical Methods

We will conduct independent *t*-test with the continuous variables and chi-square test with the categorical variables to check for differences at baseline. Treatment differences will be analyzed using hierarchical linear modeling (HLM; (Raudenbush and Bryk, 2002), hence all available data will be used. Thus, a patient with only data at admission can be included in an analysis and contribute to the estimation of model parameters (Kwok et al., 2008). Effect sizes (Cohen’s *d*) for HLM-analysis will be performed according to Feingold (2009). Interpretations will be based on the categorization of Cohen (1988).

Frequent longitudinal measurements in the treatment period will be analyzed disaggregating between patient effects (i.e., a patients standing relative to other patients) from the effect of individual patients development throughout therapy (i.e., a particular patients deviation from that patients expected level at a specific time point) using longitudinal mixed models (Curran and Bauer, 2011). This disaggregation is able to examine intra-individual process of change that is not contaminated with between-person variability (Paccagnella, 2006; Enders and Tofighi, 2007; Curran and Bauer, 2011). Within effects gives information on the level of the individual patient, making research findings directly applicable for therapists working with a specific patient.

Moderator variable will be included to analyze whether any treatment effects are modified by trauma or ED diagnosis. If treatment arms do not differ in outcome, combined latent class growth curve modeling will be conducted to analyze reasons for individual differences at baseline and in the rate of change across time. The multiple imputation procedure in SPSS will be used to impute missing data, if the data is missing at random.

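### Randomisation is blocked on trauma, but the only written model for the main treatment comparison has no trauma term, so its test is mildly conservative if trauma is prognostic beyond baseline.

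*Protocol article*

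**What the plan says.** Protocol article, Randomization: "A blocked randomization procedure will be used to ensure that there will be assigned an equal number of patients with trauma and non-trauma". The balance meant is between the two treatment arms, and the same section fixes the allocation ratio: "The probability for each patient to end up in any of the two conditions will be kept constant at 0.5". Trauma status is set by CTQ thresholds (Childhood Trauma Questionnaire section), and Table 2 places the CTQ at the initial assessment.

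Power Estimation: "The primary outcomes in the two groups were compared using analysis of covariance (ANCOVA) with pre-treatment values as the covariate". Model (1), written out there, regresses the post-treatment score on treatment and the pre-treatment score. Model (2) adds trauma and treatment by trauma, but for a different question: "The effect of interest, the Treatment by Trauma interaction, will be estimated by the increase in explained variance".

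Statistical Methods: "Treatment differences will be analyzed using hierarchical linear modeling", with no covariates listed. Trauma appears only in the sentence "Moderator variable will be included to analyze whether any treatment effects are modified by trauma or ED diagnosis".

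No section adjusts the main comparison for the stratum.

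**The concern.** When allocation is balanced within a prognostic factor, that factor's contribution cancels out of the treatment contrast. If the model then omits the factor, its variance stays in the residual, and the standard error is computed as if the balancing had not been done. The reported interval is wider than the design warrants and the test rejects less often than its nominal level.

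The Introduction gives some reason to expect trauma to matter: "The highest probability of poor treatment outcomes in patients with ED has been observed in those who experienced childhood sexual abuse". At stake is a main comparison that understates its own precision. This has a further consequence, because Statistical Methods switches to latent class growth modelling if the arms do not differ in outcome, and a conservative test makes that branch slightly more likely.

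**Working it through.** **Inputs from the protocol article.** Power Estimation: d = 0.5, R² increase 0.06, alpha 0.05, power 0.80, 62 patients per arm for model (1), total N = 144. Randomization: 1:1 allocation, blocked on trauma. Abstract: about half the patients have childhood trauma.

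**Assumptions.** The test is two-sided (sidedness is not stated). Balance within strata is exact. The share r of the model (1) residual variance that trauma explains is not given, so it is run at 0, 0.05, 0.10 and 0.15. The effect d = 0.5 is on the model (1) residual SD.

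**Step 1: the plan's own figure.** f² = 0.06/0.94 = 0.0638. The F test with 1 numerator df and noncentrality f²N first reaches power 0.80 at N = 125, that is 62.5 per arm. The stated 62 per arm (N = 124, power 0.797) therefore reproduces. Taking d = 0.5 exactly gives f² = 0.25/4 = 0.0625 and N = 128, or 64 per arm. The steps below use this second value.

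**Step 2: standard errors.** On the model (1) residual SD, the reported SE is 2/√N: 2/√144 = 0.1667 and 2/√124 = 0.1796. With balance inside strata, the true SE is √(1 − r) times this, whether or not trauma is in the model. For r = 0.05, 0.10 and 0.15 the factor √(1 − r) is 0.975, 0.949 and 0.922. Model (1) thus overstates the SE by 2.6%, 5.4% and 8.5% (1/√(1 − r) = 1.026, 1.054, 1.085).

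**Step 3: type I error of model (1).** 2 × [1 − Φ(1.96/√(1 − r))].

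**Step 4: power on one consistent basis.** Both models have the same true SE and differ only in the SE they report.
- Model (1): Φ[(0.5/SE − t)/√(1 − r)].
- With trauma: Φ[0.5/(SE·√(1 − r)) − t].

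At N = 144, 0.5/0.1667 = 3.00 and t = 1.977. At N = 124, 0.5/0.1796 = 2.784 and t = 1.980. Example at N = 144, r = 0.10: model (1) gives Φ(1.023/0.949) = 0.86; with trauma, Φ(3.162 − 1.977) = 0.88.

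| r | Type I error, model (1) | Power N = 144: model (1) → with trauma | Power N = 124: model (1) → with trauma |
|---|---|---|---|
| 0 | 5.0% | 0.85 → 0.85 | 0.79 → 0.79 |
| 0.05 | 4.4% | 0.85 → 0.86 | 0.80 → 0.81 |
| 0.10 | 3.9% | 0.86 → 0.88 | 0.80 → 0.83 |
| 0.15 | 3.4% | 0.87 → 0.90 | 0.81 → 0.85 |

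Before rounding, the gains are about 1, 2 and 3 points at N = 144, and 1.4, 2.8 and 4.2 points at N = 124.

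**Step 5: simulation check.** 10,000 trials per scenario at N = 144, balanced within two equal strata. At r = 0.10, model (1) reported a mean SE of 0.167 against a true SE of 0.158, with type I error 0.037. With trauma added, reported and true SE agreed, and across the range of r type I error was 0.047 to 0.051. The empirical SE of the estimate was the same in both models to within 0.0002.

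**The case against.** Model (1) is not clearly the primary analysis. It stands under Power Estimation, as part of a rough assessment of power, while Statistical Methods names a hierarchical linear model whose covariates an article may properly leave to the analysis plan. This stands in part. It cannot be said that the final analysis will omit trauma, and the arithmetic above applies to ANCOVA, not directly to a treatment-by-time effect. But the Power Estimation text does tie the primary outcomes to ANCOVA, the equation is written out without the stratum, and the two sections conflict.

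The prognostic strength is also assumed. The Introduction's evidence concerns childhood sexual abuse and early exposure to violence. The stratum is broader: any one of five CTQ thresholds, including emotional neglect. Nothing shows that this composite predicts post-treatment EDE once baseline EDE is in the model. This stands, which is why zero belongs in the range.

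A reader might infer that omitting trauma loses real precision, equivalent to 5%, 11% or 18% of patients (from 1/(1 − r) − 1). The documents do not support that. Balanced blocking already secures the precision, and only the reported SE is wrong. Nor is the factor ignored altogether, since trauma is a main effect in model (2).

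**Conclusion.** The point holds in a limited form. The written main-comparison model does not follow the randomisation, and if trauma is prognostic beyond baseline, its SE and interval are too wide and its test conservative. For r up to 0.15, type I error falls to no less than about 3.4%, and the power forgone is at most about 3 points at the planned N = 144 or 4 points at N = 124. At r = 0 nothing is lost. Power at N = 144 stays above 0.80 with either model, before dropout, which the article does not quantify.

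These sizes rest on the assumed r, on near-exact balance within strata and on ANCOVA being the model used. A reader might also infer bias or a false-positive risk; neither follows, because the only error is towards caution. The change is worth making because it is nearly free, not because the trial's conclusions are endangered.

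**What to change.** Reconcile Statistical Methods (HLM) with Power Estimation (ANCOVA) by naming one primary model, and include the trauma stratum, as randomised, as a fixed effect in it.
- If ANCOVA is primary: Post = a + b1 Treatment + b2 Pre + b3 Trauma.
- If HLM is primary: include Trauma and Trauma by time.
- Include the stratum likewise in the analysis of the second primary outcome, EDE below 1.74. That outcome is binary, so it needs its own stated model.
- Keep model (2) for the interaction.

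The cost is one degree of freedom, plus one more for the time term if time is linear. No new data are needed, because trauma status must be known before a patient can be allocated.

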#### Inclusion Criteria

In order to be eligible to participate in this study, a participant must meet all of the following criteria: (1) adult inpatients (from age 18 years) with an ED diagnosis: AN, BN, and OSFED (EDNOS), according to the eating disorder examination-interview and (2) provision of informed consent.

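### The primary comparison is adjusted for the pre-treatment score only, leaving out trauma (the blocking factor) and ED diagnosis: no bias, but precision is given up at almost no saving

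*Protocol article*

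**What the plan says.** - **Allocation** (Protocol article, Randomization). Blocking is on trauma status, so that each arm is "assigned an equal number of patients with trauma and non-trauma to each condition". Allocation is 1:1. ED diagnosis is not a blocking factor.
- **Population** (Inclusion Criteria). Patients enter "with an ED diagnosis: AN, BN, and OSFED (EDNOS"), established by interview. Diagnosis is therefore a three-level factor known at entry.
- **Primary comparison** (Power Estimation). The primary outcomes are "compared using analysis of covariance (ANCOVA) with pre-treatment values as the covariate". Model (1) contains treatment and the pre-treatment score. Model (2) adds trauma and its interaction with treatment, in order to test that interaction. Diagnosis is in neither.
- **Other statement of the analysis** (Statistical Methods). "Treatment differences will be analyzed using hierarchical linear modeling", with no covariates listed.
- **Moderators** (Statistical Methods). "Moderator variable will be included to analyze whether any treatment effects are modified by trauma or ED diagnosis".
- **Baseline comparison** (Statistical Methods). Continuous variables get t-tests, and the plan adds a "chi-square test with the categorical variables to check for differences at baseline". No consequence of a significant or non-significant result is stated.

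**The concern.** Two baseline factors are singled out by the plan itself: trauma, used to form the blocks, and ED diagnosis, which joins trauma as a possible moderator. Neither is in the model written out for the main treatment comparison. If either factor predicts the post-treatment EDE score at a given pre-treatment score, leaving it out puts explainable variation into the error term. For diagnosis, which is not blocked, a chance difference in case mix between the arms also stays in the estimate. Both factors are collected anyway, so adjusting needs no new data.

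The only check on case mix that the plan describes is a set of significance tests between arms. Under sound randomisation any baseline difference is due to chance, so a p-value does not tell the reader whether the difference matters for the outcome.

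**Working it through.** **1. The plan's own figure.** Inputs from Power Estimation: alpha 0.05, power 0.80, increase in R² of 0.06. With an F test on 1 numerator degree of freedom and noncentrality f²·N:

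- f² = 0.06/0.94 = 0.0638 gives N = 125, or 62.5 per arm. The plan states 62, so its figure reproduces and is not in dispute.
- Without rounding, d = 0.5 gives R² = 0.25/4.25 = 0.0588 and f² = 0.0625, hence N = 128. This slightly more cautious value is used below.

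**2. What adjustment is worth.** Let q be the share of residual variance (after treatment and pre-treatment score) that diagnosis explains. The documents do not give q, so a range is assumed. Adjustment changes f² to 0.0625/(1 − q), and the noncentrality at N = 144 is 144 × f².

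| q (assumed) | f² | Noncentrality | Power at N = 144 | N for 80% power |
|---|---|---|---|---|
| not adjusted | 0.0625 | 9.00 | 84.6% | 128 |
| 0 | 0.0625 | 9.00 | 84.6% | 128 |
| 0.05 | 0.0658 | 9.47 | 86.4% | 122 |
| 0.10 | 0.0694 | 10.00 | 88.1% | 116 |

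Diagnosis takes 2 degrees of freedom and trauma 1, so the residual degrees of freedom fall from 141 to 138. The third degree of freedom leaves every power figure in the table unchanged to one decimal. Any variance that trauma explains would come on top and is not counted here.

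**3. Chance imbalance in diagnosis.** Inputs: 72 per arm (144/2) and an assumed share of 30% to 50% for one diagnosis, such as AN. The standard error of the difference in shares is √(2p(1 − p)/72).

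- p = 0.30: 0.076, 95% range ±15.0 percentage points.
- p = 0.50: 0.083, 95% range ±16.3 percentage points.

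The effect on the treatment estimate is the imbalance times the outcome difference between diagnoses at equal pre-treatment score. If that difference is 0.5 SD (assumed), a typical imbalance of one standard error (about 0.08) shifts the estimate by 0.08 × 0.5 = 0.04 SD. An imbalance at the 95% limit (about 0.16) shifts it by 0.08 SD. For comparison, the 95% half-width of the treatment estimate is t(0.975; 142) × √(2/72) = 0.33 SD, and that interval already allows for such shifts.

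**4. What the baseline tests can show.** At 72 per arm, a chi-square test has about 23% power for shares of 45% against 35%, so a 10-point difference usually passes unnoticed. Conversely, 10 independent tests under perfect randomisation give at least one p < 0.05 with probability 1 − 0.95¹⁰ = 40%. The plan does not state the number of tests. Its scales overlap in content, and positive correlation among the tests would lower this probability, so it is only an illustration.

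**The case against.** The strongest reply is that nothing here is invalid. Randomisation makes the comparison adjusted only for the pre-treatment score unbiased, and its standard error already covers chance differences in diagnosis. **This stands.** A reader might infer that the primary estimate is biased, or that diagnosis had to be a blocking factor. The documents support neither: leaving diagnosis out of the blocks is a legitimate design choice.

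Second, the plan asks whether diagnosis modifies the treatment effect. That is not a statement that diagnosis predicts the EDE score, and a main effect does not answer the moderation question. The section on CBT content calls the specific diagnosis irrelevant to treatment, and the extra work on weight regain under Common Content applies to both arms and is not tied to the EDE score. **This stands too**, which is why q is a range that includes zero. It does not remove the point, since adjustment loses nothing noticeable when q is zero.

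Third, model (1) appears under Power Estimation, while Statistical Methods names HLM, and an article may leave a covariate list to a fuller document. **This stands in part.** The article does not settle which model is primary, but it states that the primary outcomes are compared by ANCOVA and writes out the equation with one covariate. The recommendation must therefore apply to whichever model is primary.

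Finally, a reader might infer that covariates will be picked from the baseline tests. The text states no such rule, so that harm is a possibility and not a plan.

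**Conclusion.** The point holds as a modest one about efficiency and prespecification. The main comparison, as written, adjusts for the pre-treatment score alone and omits both the factor used for blocking and the other factor the plan names as a possible moderator. No stated figure becomes wrong and no bias follows.

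The gain in power for d = 0.5 at N = 144 runs from nil to about 3.5 percentage points (88.1 − 84.6) as the assumed share of residual variance explained by diagnosis goes from 0% to 10%. That share, the diagnostic mix and the outcome difference between diagnoses are all assumptions. The calculation is for the ANCOVA form; an HLM would give somewhat different numbers, but the direction is the same. The baseline tests are a minor reporting matter and change no planned treatment estimate.

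**What to change.** 1. In Statistical Methods, state one primary model for the continuous EDE global score, HLM or ANCOVA, and prespecify in it the pre-treatment score, trauma status (the blocking factor) and ED diagnosis (AN, BN, OSFED) as fixed main effects. The moderator analyses stay separate.
2. Replace the t-tests and chi-square tests between arms at baseline with means, standard deviations and proportions by arm, and say that covariates are fixed in advance and do not depend on observed imbalance.

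Cost: wording, and about 3 degrees of freedom (1 for trauma, 2 for diagnosis). No new data, no change to randomisation and no change to the sample size.
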